#### Sample size calculation

The primary outcome is fear of falling, measured by the FES‑I. As no MCID^2^ has been established for stroke patients, the MCID was estimated as 1.2 × the MDC (MDC^3^ = 6.69) based on previous studies [28,32].

Based on the standard deviation (SD) reported in the study by Molhemi et al. [9]., and according to the formula, sampsi 40.9 48.9, sd1(8.4) sd2(10.8) pre[1] post[1] r0(0.6) r1(0.6) alpha (0.05) power (0.8), assuming α = 0.05, power = 80%, and a pre–post correlation of 0.6, the calculated sample size was 16 participants per group, accounting for a 15% dropout rate [8,33].

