### Inclusion and exclusion criteria

32 stroke patients will be recruited for this study. inclusion criteria: Age between 40 and 70 years [21]. 2. Confirmed diagnosis of unilateral ischemic stroke in the subacute phase (3–6 months post-onset) [6] 3. Ability to walk independently for a minimum of 10 m, potentially with the assistance of a single standard walking aid [22]. 4. Hospital Anxiety and Depression Scale (HADS) score < 16 to ensure participants’ ability to cooperate and to exclude cases of severe depression [23]. 5. Cognitive screening score ≥ 21 on the Mini-Mental State Examination (MMSE) [24]. 6. Spasticity severity of the ankle dorsiflexor group, according to the Modified Ashworth Scale (MAS), on the injured side 2 or less [25]. Exclusion Criteria: 1. Significant orthopedic, vestibular, or cardiovascular conditions precluding safe gait training. 2. Presence of implanted metallic devices, pacemakers, deep brain stimulators. 3. Presence of major neurological comorbidities or psychiatric disorders. Participant recruitment will take place through the inpatient neurological rehabilitation wards of Rofeideh Hospital and affiliated units of URSSH. Throughout all treatment sessions, if the participant experiences severe fatigue, blurred vision, dizziness, or any other unexpected adverse sensation, the intervention will be immediately discontinued. The trial will also be stopped for any participant who shows sensitivity or intolerance to tDCS, expresses unwillingness to continue participation, or develops any of the exclusion criteria during the study period.

A blinded assessor will evaluate outcomes at baseline and after ten physiotherapy sessions, with assessments scheduled to avoid unblinding. The study follows the Declaration of Helsinki, written informed consent will be obtained, and participants’ demographic and clinical information will be recorded after randomization.

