#### Data analysis

data normality will be assessed with the Shapiro–Wilk test. Depending on distribution, paired t‑tests or Wilcoxon tests will be applied for within‑group comparisons, and 2 × 2 repeated‑measures ANOVA will be used for between‑group analyses. Between-group differences were analyzed using ANCOVA, with time since stroke (post-onset duration) included as a covariate to account for potential differences in recovery status. Statistical analyses will be performed in SPSS v26, with significance set at p < 0.05.

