## Limitations

Although electrode placement followed the international 10–20 EEG system, due to electrode size and proximity to the primary motor cortex (M1), some degree of current spread may have occurred. While the power analysis suggests 16 participants per group, the relatively small sample size may limit the generalizability of the findings; therefore, the results should be interpreted with caution.

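### Sixteen per group does not contain the stated 15% dropout allowance; with that loss the trial falls below its stated 80% power

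*Protocol article*

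**What the plan says.** All of the inputs are in the protocol article, Statistics, Sample size calculation. The printed command begins "sampsi 40.9 48.9, sd1(8.4) sd2(10.8" and continues "pre[1] post[1] r0(0.6) r1(0.6) alpha (0.05) power (0.8" (closing brackets omitted here). It therefore uses one baseline and one follow-up measurement with a correlation of 0.6 in each group. The 8-point difference is close to the estimated MCID, 1.2 × 6.69 = 8.03. The section then states the result: "the calculated sample size was 16 participants per group, accounting for a 15% dropout rate". It gives no separate number of evaluable patients, and the command contains no dropout term.

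Two other sections carry the figure forward. Inclusion and exclusion criteria says "32 stroke patients will be recruited for this study". Limitations says "While the power analysis suggests 16 participants per group".

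The Data analysis section gives the test level only as "with significance set at p < 0.05". For between-group comparison it names both a 2 × 2 repeated-measures ANOVA and an ANCOVA whose only named covariate is time since stroke.

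**The concern.** The article presents 16 per group as a number that already absorbs 15% dropout at 80% power. If 16 is close to the number needed with nobody lost, the allowance is nominal and the stated power applies only to a nearly complete trial. In a trial of 32 patients, each lost patient matters. A non-significant result would be read as coming from a study with 80% power to detect 8 FES-I points after the expected losses, when its real power was lower.

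**Working it through.** **Inputs** (Sample size calculation unless noted): difference 48.9 − 40.9 = 8.0; SDs 8.4 and 10.8; correlation r = 0.6; alpha 0.05; power 0.80; dropout 15%; 1:1 allocation (Random allocation). Sidedness is not stated. Two-sided is assumed, because the printed command requests no one-sided test.

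**Formula**, normal approximation, per group:

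n = (z₀.₉₇₅ + z₀.₈₀)² × (SD₁² + SD₂²) / difference² × f

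The factor f depends on the analysis: 1 for post scores alone, 2(1 − r) = 0.8 for change scores, and 1 − r² = 0.64 for ANCOVA on baseline.

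SD₁² + SD₂² = 70.56 + 116.64 = 187.2, so n = (1.96 + 0.8416)² × 187.2/64 × f = 22.96 × f.

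**Trying to reproduce 16 with 15% dropout**

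| Analysis | f | n before rounding | Evaluable per group | After 15% loss, n/0.85 |
|---|---|---|---|---|
| ANCOVA on baseline | 0.64 | 14.69 | 15 | 17.6 → 18 |
| Change score | 0.80 | 18.37 | 19 | 22.4 → 23 |
| Post score | 1.00 | 22.96 | 23 | 27.1 → 28 |

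Other routes for the most favourable row (ANCOVA):
- Multiplying instead of dividing: 15 × 1.15 = 17.25 → 18.
- Inflating the unrounded figure: 14.69/0.85 = 17.3 → 18; 14.69 × 1.15 = 16.9 → 17.
- Using 8.03 as the difference: 14.59 → 15, then 18 as before.

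No two-sided route that rounds up gives 16. The stated 16 is one above the ANCOVA number before dropout.

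**What 16 allows for:** 1 − 15/16 = 6.25% loss, or 1 − 14.69/16 = 8.2% against the unrounded requirement.

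**Power after 15% loss:** 16 × 0.85 = 13.6 evaluable per group. For ANCOVA the standard error is √(187.2 × 0.64/13.6) = 2.97. Then 8/2.97 − 1.96 = 0.73 to 0.74, and power is 76.9%.

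| Analysis | Power, 16 evaluable (normal / t) | Power, 13.6 evaluable (normal / t) | Difference detectable at 80%, 13.6 evaluable (normal) |
|---|---|---|---|
| ANCOVA on baseline | 83.2% / 80.7% | 76.9% / 73.5% | 8.3 |
| Change score | 74.4% / 71.5% | 67.4% / 64% | 9.3 |
| Post score | 64.8% / 61.8% | 57.8% / 54–55% | 10.4 |

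The last column is 2.8016 × √(187.2 × f/13.6).

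With whole patients, ANCOVA power is 78.1% with 14 completers per group and 75.0% with 13 (normal), or 74.8% and 71.4% (t).

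**The t-based reading** does not help the stated figure. ANCOVA power is 77.9% with 15 evaluable per group and 80.7% with 16. On that basis 16 is the number needed with no dropout at all.

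**The case against.** - **The allowance may have been applied and then lost in rounding.** If 14.69 is cut to 14, then 14 × 1.15 = 16.1 and 14/0.85 = 16.5, and both become 16 if cut again. The article prints no evaluable number, so this cannot be excluded as the origin of the figure. It does not rescue the statement: rounding down twice still leaves 13.6 per group after 15% loss, with power below 80%.
- **The hypothesis is directional.** A one-sided ANCOVA would need 12 evaluable per group, or 15 with dropout, which 16 covers. But no one-sided test is stated and the command does not ask for one. The conclusion does rest on the two-sided assumption.
- **The shortfall is small.** By the normal approximation, ANCOVA power falls short by about 2 to 5 points, and the number by two patients per group. This is true. The lower figure of 73% partly reflects the change to a t-based calculation, since 15 per group gives only 77.9% on that basis. The two bases should be labelled and kept apart.
- **Baseline adjustment is not secured by the text.** The Data analysis section names only time since stroke as the ANCOVA covariate, and the group-by-time test of the repeated-measures ANOVA is a change-score comparison. This also stands, and it makes the gap larger: 23 per group with dropout against 16.
- **Limitations mentions neither dropout nor 80% power.** Correct. It repeats the 16 and needs only a consistent wording.

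**Conclusion.** The statement is wrong as written. From the article's own inputs, on a two-sided test and the most favourable analysis, 15 evaluable patients per group are needed and 18 must be randomised to absorb 15% loss. Sixteen absorbs about 6%. With 15% loss, power for 8 points is 76.9% (normal) or 73.5% (t) for baseline-adjusted ANCOVA, and 67% or 64% for a change-score test. The shortfall is 2 per group (4 in total) in the best case and 7 per group for the change-score test.

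This assumes a two-sided 0.05 level and that the stated SDs and correlation hold in this population. It does not depend on which inflation formula is used, or on whether the difference is 8.0 or 8.03.

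**What to change.** In Sample size calculation, replace the claim with one that names the analysis and the basis. For example:

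> On a two-sided 0.05 test with ANCOVA adjusting for baseline FES-I, 15 evaluable patients per group are needed for 80% power (normal approximation). Randomising 16 per group allows for about 6% loss. With 15% loss, power is about 77% by the normal approximation and about 73% by a t-based calculation.

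That wording is valid only if the primary analysis adjusts for baseline FES-I, which Data analysis should then say. If the primary test is the group-by-time term of the repeated-measures ANOVA, report 67% and 64% instead. Bring the sentence in Limitations into line.

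This costs wording only. It needs no extra enrolment, and the stated power becomes slightly less favourable. Protocol validation says recruitment is under way and no outcome data exist, so the correction can be made before results are known.

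If the sponsor wants to keep both 80% power and the 15% allowance, the number that follows from the stated inputs is 18 per group (36 in total) by the normal approximation. By the t-based calculation, 16/0.85 = 18.8 gives 19. Either choice means recruiting beyond the planned 32.

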## Protocol validation

Although the validity of this randomized controlled trial protocol is supported by existing scientific evidence and clinical guidelines, Standardized outcome measures with established validity and reliability in the stroke population (FES‑I, Mini‑BESTest and 10MWT) are employed to assess fear of falling, balance, and walking ability, this clinical study is still ongoing, with participant recruitment and intervention currently in progress; therefore, outcome data for empirical validation have not yet been generated.

## Limitations

Although electrode placement followed the international 10–20 EEG system, due to electrode size and proximity to the primary motor cortex (M1), some degree of current spread may have occurred. While the power analysis suggests 16 participants per group, the relatively small sample size may limit the generalizability of the findings; therefore, the results should be interpreted with caution.

## Data Availability

No data was used for the research described in the article.
